**2.3.6 Baseline assessments**

**2.3.6.1 Physical activity assessment**

Physical activity will be objectively measured using a triaxial accelerometer worn on the participant’s dominant thigh for 7 consecutive days, including at least 2 weekend days, in accordance with published guidelines for accelerometry in older adults.
^
26
^ The device will record total activity counts and time spent in sedentary, light, moderate, and vigorous-intensity physical activity, expressed as metabolic equivalent of task (MET) minutes per week. In addition, the validated Global Physical Activity Questionnaire (GPAQ) will be administered by a trained research assistant to capture self-reported physical activity across three domains (work, transport, and leisure) and sedentary time.
^
27
^ The GPAQ requires approximately 5–10 minutes to complete and will be administered after detailed verbal and written instructions are provided.

**2.3.6.2 Anthropometric and metabolic measurements**

Height will be measured to the nearest 0.1 cm using a calibrated stadiometer, and body weight will be recorded to the nearest 0.1 kg using a digital weighing scale, with participants barefoot and in light clothing. BMI will be calculated as weight (kg) divided by height squared (m
^2^). Waist circumference will be measured at the midpoint between the lowest rib and the iliac crest. Fasting blood glucose and HbA1c will be recorded from participants’ clinical laboratory reports.

**2.3.6.3 Vascular assessment: carotid doppler ultrasonography**

Carotid Doppler ultrasonography will be performed with participants seated following a 10-minute rest period. A 7–15 MHz multifrequency linear array transducer will be used with a high-resolution B-mode ultrasound machine. Peak systolic velocity (PSV), end-diastolic velocity (EDV), and resistive index (RI) of the common carotid artery (CCA) will be recorded bilaterally. Carotid artery diameter will be measured at the far wall of the CCA, 1 cm proximal to the carotid bifurcation. Endothelial shear stress will be calculated from the velocity and diameter values. All measurements will be performed by the same trained sonographer throughout the study to minimize inter-rater variability. A minimum of three consecutive cardiac cycles will be averaged for each measurement.

**2.3.6.4 Neuroimaging protocol**

All MRI data will be acquired using the 3-Tesla United Imaging uMR 780 scanner at the Department of Radiodiagnosis and Imaging, Kasturba Hospital, Manipal. Participants will be positioned supine with their head immobilized using foam padding to minimize motion artifacts. A 32-channel head coil will be used for all sequences. The imaging protocol comprises four sequences as follows.

**Sequence 1: Structural MRI — Volumetric brain morphometry**

A T1-weighted three-dimensional Fast Spoiled Gradient Echo (FSPGR) sequence will be acquired for voxel-based morphometry (VBM) analysis. Imaging parameters will include repetition time (TR) = 7.8 ms; echo time (TE) = 3.1 ms; inversion time (TI) = 1010 ms; flip angle = 10°; field of view (FOV) = 256 × 256 mm; voxel size = 1 × 1 × 1 mm isotropic; 176 contiguous axial slices. Post-processing and analysis will be performed in MATLAB (MathWorks) using the SPM12 toolbox (Wellcome Centre for Human Neuroimaging, UCL) with the CAT12 (Computational Anatomy Toolbox, version 12) extension.
^
28
^ The standard CAT12 cross-sectional pipeline will be applied, comprising: (1) bias-field correction and denoising; (2) unified segmentation into grey matter (GM), white matter (WM), and cerebrospinal fluid (CSF) tissue classes; (3) diffeomorphic registration to the MNI152 standard space using the Geodesic Shooting algorithm (DARTEL); and (4) modulation of segmented images to preserve absolute tissue volumes following normalisation. For ROI-based segmentation, the CAT12 automated parcellation will be applied using the Automated Anatomical Labeling (AAL3) atlas, extracting absolute and relative grey matter volumes for bilateral regions of interest, including the hippocampus, entorhinal cortex, prefrontal cortex, anterior cingulate cortex, insula, and parietal association cortex. Total intracranial volume (TIV) will be extracted from the Jacobian determinant maps and used as a covariate in all volumetric analyses to account for individual differences in head size.

**Sequence 2: Diffusion tensor imaging (DTI)**

White matter microstructural integrity will be assessed using a single-shot echo-planar DTI sequence acquired with participants in the supine position. Acquisition parameters will include TR = 4237 ms; TE = 87.3 ms; b-values = 0 and 1000 s/mm
^2^; 32 non-collinear diffusion gradient directions; FOV = 220 × 220 mm; voxel size = 1.72 × 1.72 × 2 mm; 45 axial slices; and GRAPPA acceleration factor = 2. DTI data will be pre-processed and analyzed using ExploreDTI.
^
29
^ Pre-processing will include: (1) signal drift correction; (2) Gibbs ringing suppression; (3) eddy current and subject motion correction using a robust tensor estimation approach with outlier rejection (REKINDLE algorithm); and (4) brain extraction. The diffusion tensor will be estimated at each voxel using a non-linear least squares fitting procedure. ROI-based tractography will be performed using deterministic streamline tractography (Euler integration, step size = 1 mm, FA threshold = 0.20, maximum turning angle = 30°). White matter tracts of primary interest — including the corpus callosum, corticospinal tract, superior longitudinal fasciculus, inferior fronto-occipital fasciculus, cingulum, and uncinate fasciculus — will be reconstructed using atlas-based ROI placement guided by the JHU white matter atlas. Mean values of fractional anisotropy (FA), mean diffusivity (MD), radial diffusivity (RD), and axial diffusivity (AD) will be extracted per tract per participant for between-group and pre-post comparisons.

**Sequence 3: Resting-State functional MRI (rs-fMRI)**

Resting-state BOLD (Blood Oxygenation Level-Dependent) fMRI will be acquired using a gradient-echo echo-planar imaging (EPI) sequence. Parameters: TR = 3000 ms; TE = 30 ms; flip angle = 80°; FOV = 230 × 230 mm; voxel size = 3.5 × 3.5 × 3.5 mm; 40 interleaved axial slices. Participants will be instructed to lie still with eyes open, fixated on a cross projected on a screen, and to refrain from deliberate mental activity. RS-fMRI data will be preprocessed using the CONN toolbox (v22.a) in MATLAB, including slice-timing correction, realignment, co-registration to T1 structural image, normalization to MNI space, and spatial smoothing (6 mm FWHM Gaussian kernel).
^
30
^ Independent component analysis (ICA) will be used to identify and remove noise components (motion, physiological artifacts). Default mode network (DMN), frontoparietal network (FPN), and salience network (SN) connectivity will be examined as primary functional outcomes using seed-based and ICA-based approaches.

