**2.3.4 Exclusion criteria**
•Presence of neurological or psychiatric conditions known to affect brain morphology or cognitive function (e.g., Parkinson’s disease, major depressive disorder, schizophrenia, prior stroke or traumatic brain injury).•History of neurodegenerative disease (e.g., Alzheimer’s disease, vascular dementia).•Type 1 diabetes mellitus or secondary forms of diabetes.•Active malignancy or any systemic illness likely to confound neuroimaging or cognitive assessments.•Contraindications to MRI (metallic implants, claustrophobia, cardiac pacemakers).•Current or recent (within 6 months) regular yoga practice (≥ 2 sessions per week).•Severe hearing or visual impairment precluding cognitive testing.

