**Step 2: Integration and selection of practices**

Yoga practices identified as having therapeutic potential for vascular health, brain structural and functional improvement, and cognitive enhancement will be collated. These will be evaluated for their safety and practicability in the context of the target population’s physical limitations, comorbidities (osteoarthritis, reduced balance, cardiorespiratory deconditioning), and age-related contraindications to inversions, deep twists, and high-load postures. Selected practices will encompass asanas (physical postures), pranayama (breath regulation), and dharana/dhyana (mindfulness and concentration techniques).

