**2.5.5 Intervention: frequency and duration**

Participants will be asked to practice yoga for at least 5 days per week for 6 months. Each session will be approximately 45–60 minutes in duration, incorporating a warm-up asana sequence (10 minutes), core therapeutic asanas (25–30 minutes), pranayama (10 minutes), and relaxation/dharana (5–10 minutes).

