**2.5.9 Outcome measures**

**Primary outcomes**
•Change from baseline to 6 months in carotid artery hemodynamic parameters.•Change from baseline in regional grey matter volume and TIV.•Change from baseline in DTI metrics of major white matter tracts.•Change from baseline in resting-state functional connectivity of the DMN, FPN, and SN (rs-fMRI).

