## 5 Discussion

The current protocol describes a comprehensive, three-phase investigation designed to characterize alterations in the vascular, structural, and functional brain networks associated with obesity and T2DM in elderly adults, and to evaluate the neuromodulatory potential of a validated, structured yoga intervention using multimodal MR neuroimaging. To our knowledge, this is the first study to employ a concurrent multi-sequence MRI protocol, encompassing T1-weighted VBM with CAT12 ROI segmentation, ExploreDTI-based white matter tractography, resting-state fMRI, and carotid Doppler ultrasonography, specifically in an elderly obese-diabetic population undergoing a structured yoga intervention.

The decision to adopt a three-phase sequential design reflects the complexity of the research question and the need to establish a robust methodological foundation before proceeding to the intervention. Phase 1 addresses the critical need for a detailed neurobiological characterization of the target population prior to any therapeutic application, providing both the baseline comparator data and the evidence base that informed the structure of the Phase 3 intervention. Phase 2 ensures that the yoga module delivered in Phase 3 is not only scientifically grounded but also culturally appropriate, practically feasible, and formally validated for safety and content, a step conspicuously absent in most existing yoga intervention trials, which have frequently relied on ad hoc or unstandardized practice regimens. Phase 3 then applies the validated module in a prospective pre-post design, enabling within-subject quantification of neuroplastic change across all imaging and cognitive domains characterized in Phase 1.

Several limitations of the present study design merit acknowledgment. The study population is drawn from a single tertiary hospital in coastal Karnataka, which may limit the generalisability of the findings to other regions of India and to populations with differing levels of yoga familiarity, dietary patterns, and genetic risk profiles for T2DM and obesity. Second, the 6-month intervention window, while among the longest in the yoga-neuroimaging literature, may be insufficient to detect macrostructural volumetric changes in highly atrophied regions; longer follow-up periods and multi-site designs should be incorporated in future work.

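### Phase 3 resting-state connectivity change could partly be a temporary practice state, because the repeated scan instruction does not rule out trained breathing or relaxation and the design has no comparison arm

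*Protocol article*

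**What the plan says.** - **Scan instruction** (2.3.6.4, Sequence 3). Participants lie still with eyes open, "fixated on a cross projected on a screen, and to refrain from deliberate mental activity".
- **Baseline exposure** (2.3.4). One exclusion reads "Current or recent (within 6 months) regular yoga practice (≥ 2 sessions per week", so participants first meet the instruction without a recent regular practice.
- **Training.** The module is to include "dharana/dhyana (mindfulness and concentration techniques" (2.4.2, Step 2). Each session contains "pranayama (10 minutes), and relaxation/dharana (5–10 minutes", and participants are asked to "practice yoga for at least 5 days per week for 6 months" (2.5.5).
- **Second scan** (2.5.8). The whole imaging protocol is repeated, so the same instruction applies.
- **Design** (2.5.2). Pre-test post-test; no comparison arm is described.
- **Outcome** (2.5.9). A primary outcome is "Change from baseline in resting-state functional connectivity of the DMN, FPN, and SN (rs-fMRI".
- **Analysis** (2.5.10). Paired t-tests or Wilcoxon tests, and mixed models adjusted for age, sex, baseline physical activity, HbA1c and medication use.
- **Interpretation** (section 5). The pre-post design is described as "enabling within-subject quantification of neuroplastic change across all imaging and cognitive domains characterized in Phase 1". The limitations listed there are the single site and the length of the intervention; in-scanner state is not among them.

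**The concern.** Resting-state connectivity depends on what a person is doing during the scan as well as on lasting properties of the network. At baseline, participants have no recent regular yoga practice. At 6 months they have been taught ways of breathing, relaxing and concentrating, and they lie in the same scanner under the same words. If some use a trained technique, knowingly or not, the two scans record different conditions, and the difference enters the change score.

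Nothing else in the plan would take it out. No comparison arm is available to subtract it. None of the covariates in 2.5.10 measures mental state during the scan. The ICA step in Sequence 3 is aimed at motion and physiological noise; it may remove some breathing-related signal, but it is not designed to remove a change in mental state. At stake is how one of the four Phase 3 primary outcome groups is read: as lasting network change, or as what participants happened to be doing that day.

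**Working it through.** The plan states no figure on this point, so there is none to reproduce. The check has two parts.

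**1. Planned training between the scans** (inputs from 2.5.5, taking 6 months as 26 weeks)

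- Sessions, at minimum: 5 × 26 = 130.
- Pranayama: 130 × 10 = 1,300 min.
- Relaxation/dharana: 130 × 5 = 650 min to 130 × 10 = 1,300 min, that is 10.8 to 21.7 h.

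This shows that the techniques would be well rehearsed. It says nothing about whether anyone uses them in the scanner.

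**2. Illustration: chance of a significant paired test when nothing lasting has changed**

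Assumptions, none of them in the documents:

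- A share p of participants uses a technique at the second scan only.
- Users shift by δ = 0.4 to 0.8 SD of a single measurement; non-users do not shift.
- The pre-post correlation is r = 0.6.
- There are n = 40 pairs. Section 2.3.5 plans 40 obese-diabetic participants for Phase 1; no Phase 3 number is stated.
- The test is two-sided at 0.05, as stated for Phase 1 in 2.3.6.7.

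Formulas:

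- Spurious mean shift = p × δ.
- Variance of the change score = 2(1 − r) + p(1 − p)δ². The second term arises because only some participants shift.
- Standardised shift dz = pδ / √[2(1 − r) + p(1 − p)δ²].
- Rejection probability from the noncentral t with n − 1 degrees of freedom and noncentrality dz√n.

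With r = 0.6 the first variance term is 2 × 0.4 = 0.80. Worked example for p = 0.50 and δ = 0.8: the shift is 0.40, the variance is 0.80 + 0.25 × 0.64 = 0.96, and dz = 0.40/√0.96 = 0.408, giving a rejection probability of 0.71.

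| p | Mean shift (SD), δ = 0.4 to 0.8 | dz | Rejection probability, n = 40 |
|---|---|---|---|
| 0.05 | 0.02 to 0.04 | 0.022 to 0.044 | 0.052 to 0.058 |
| 0.10 | 0.04 to 0.08 | 0.044 to 0.086 | 0.059 to 0.083 |
| 0.25 | 0.10 to 0.20 | 0.110 to 0.209 | 0.10 to 0.25 |
| 0.50 | 0.20 to 0.40 | 0.218 to 0.408 | 0.27 to 0.71 |

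Leaving out the mixture term would overstate the last figure: dz = 0.40/√0.80 = 0.447 and a rejection probability of 0.79.

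The result depends almost wholly on p. If few participants use a technique, the error rate stays close to the nominal 5%; if half do, it does not. The documents give no basis for choosing between these.

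**The case against.** A reader might infer something stronger: that the scan instruction closely matches the exercise the module trains, so that participants will meditate in the scanner and a momentary state will be reported as neuroplasticity. The documents do not support this, for three reasons.

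- They describe dharana and dhyana only in general terms, and the session time is given as "relaxation/dharana (5–10 minutes", shared with relaxation. No gaze-fixation or thought-suppression technique is named, and the module is still to be developed and validated in Phase 2. The match would have to come from outside knowledge.
- Read literally, asking participants to avoid deliberate mental activity already discourages deliberate meditation.
- No results exist. A state effect is a possibility, not something the plan establishes.

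Other fair objections: eyes-open fixation is a coherent rest condition held constant across visits, the full scan script may say more than a journal article does, and any figure for the size rests on assumption.

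These points remove the claim of a close match and any claim that the instruction is wrong in itself. They leave a gap. As printed, the instruction does not mention breathing, relaxation or yoga practice, and a participant can slip into slow breathing or trained relaxation without regarding it as deliberate thought. Holding the words constant does not hold the state constant when the intervention between the two visits trains that state. In a single-arm design, the primary connectivity outcome then has no safeguard against this.

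**Conclusion.** The concern holds in a limited form. As described, Phase 3 cannot separate a temporary practice state from lasting change in its resting-state connectivity outcome, so the Discussion's wording claims more for that outcome than the design can show. This rests on the stated instruction, the stated training, the repeat of the same protocol and the absence of a comparison arm; it does not require that the trained technique resemble the instruction.

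The size is unknown. Under the assumptions above, the effect runs from negligible (about 5–8% rejection if 5–10% of participants use a technique) to serious (27–71% if half do). The scope is narrow: Phase 1, the T1 morphometry and the DTI outcomes are not affected. It is worth correcting because it touches a primary outcome and costs almost nothing before the first scan.

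**What to change.** 1. Keep the eyes-open fixation instruction and add, at both visits: *breathe as usual and do not use any yoga, breathing, relaxation or concentration practice during the scan.* Replacing the instruction with free mind-wandering is not needed; that would set a different mental condition, and nothing in the documents shows it to be more neutral.
2. Straight after each resting-state run, ask one yes/no question on whether any such practice was used, and report the proportion answering yes.
3. Show the Phase 3 connectivity change with and without those answering yes, labelled as a descriptive sensitivity analysis only.
4. State in section 5 that the rs-fMRI change cannot by itself be attributed to lasting neuroplasticity.

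**Cost.** One sentence in the scan script, one question, one extra table row and one sentence in the Discussion. The Data Availability statement says that no participant data had been collected at publication. If baseline scanning has not begun, nothing is lost; once it has, changing the wording would itself create a difference between visits.

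**Downside.** Self-report is imperfect. The exclusion conditions on something that happens after the intervention: those who answer yes may be the most adherent, and so the most likely to show real change. The sensitivity analysis can therefore be biased, and it uses fewer participants. It should inform the reading of the main result, not replace it.

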**2.3.6.7 Statistical analysis**

All statistical analyses will be performed using Jamovi. Demographic and clinical characteristics will be summarised using descriptive statistics: mean ± standard deviation (SD) for normally distributed continuous variables; median and interquartile range (IQR) for skewed data; and frequencies with percentages for categorical variables. Normality will be assessed using the Shapiro-Wilk test. Group differences in neuroimaging and cognitive outcomes will be examined using independent-samples t-tests or Mann-Whitney U tests, as appropriate. A two-way ANOVA will be used to investigate interactions between group and sex or age; a nonparametric alternative (Kruskal-Walli’s test with Dunn’s post hoc correction) will be applied when distributional assumptions are violated. Associations between neuroimaging metrics, vascular parameters, metabolic indices, and cognitive performance will be explored using Pearson’s or Spearman’s correlation coefficients and multiple linear regression models, adjusting for age, sex, years of education, and physical activity level. A significance threshold of p < 0.05 (two-tailed) will be applied throughout.

### 2.4 Phase 2

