**2.5.10 Statistical analysis**

Pre- and post-intervention neuroimaging and cognitive outcomes will be compared using paired samples t-tests (or Wilcoxon signed-rank tests for non-normally distributed data). Mixed-effects linear regression models will be used to examine the longitudinal trajectory of outcome variables, adjusting for relevant covariates (age, sex, baseline physical activity, HbA1c, and medication use). The association between intervention-induced changes in neuroimaging metrics and changes in vascular, metabolic, and cognitive outcomes will be examined using partial correlations and multivariate regression. Effect sizes (Cohen’s d and partial η
^2^) will be reported for all primary outcomes.

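### Resting-state connectivity: head motion left after realignment is handled only by ICA, and no stated test or covariate list contains a motion term

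*Protocol article*

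**What the plan says.** Connectivity of the three networks is a primary outcome in Phase 1 (section 2.3.6.6) and again in Phase 3 (section 2.5.9): "Change from baseline in resting-state functional connectivity of the DMN, FPN, and SN (rs-fMRI".

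Motion is addressed at four points, all before the statistical analysis:

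- Positioning (section 2.3.6.4): "head immobilized using foam padding to minimize motion artifacts".
- Instruction (Sequence 3): "Participants will be instructed to lie still with eyes open, fixated on a cross projected on a screen".
- Preprocessing (Sequence 3), "including slice-timing correction, realignment, co-registration to T1 structural image, normalization to MNI space, and spatial smoothing".
- Denoising (Sequence 3): "Independent component analysis (ICA) will be used to identify and remove noise components (motion, physiological artifacts".

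The tests follow in the two statistics sections. Phase 1 (section 2.3.6.7): "Group differences in neuroimaging and cognitive outcomes will be examined using independent-samples t-tests or Mann-Whitney U tests, as appropriate". The regression models there, which serve the association analyses, adjust for age, sex, education and physical activity. Phase 3 (section 2.5.10): "Pre- and post-intervention neuroimaging and cognitive outcomes will be compared using paired samples t-tests", with a Wilcoxon alternative and a mixed model adjusting for age, sex, baseline physical activity, HbA1c and medication use. Section 2.5.2 describes Phase 3 as a pre-test post-test study, with no control group.

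**The concern.** Motion that survives cleaning and correlates with measured connectivity enters the outcome as an error. If its average is the same at both visits, or in both groups, it only adds noise. If the average differs, it adds bias, and an unadjusted t-type test cannot tell that bias from a change in the brain.

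Phase 3 is the more exposed. Participants at the second scan have been in the scanner before, and they have had six months of a programme with breathing and concentration components (section 2.4.2, Step 2: "Selected practices will encompass asanas (physical postures), pranayama (breath regulation), and dharana/dhyana (mindfulness and concentration techniques"). Either could alter how still they lie. The covariates listed for the mixed model are personal characteristics and clinical variables. None measures scan quality at each visit, so none would be expected to absorb a within-person change in motion.

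At stake is the reading of a primary outcome. The Discussion presents the pre-post comparison as quantifying neuroplastic change, and a shift in scanner behaviour could be reported under that name.

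**Working it through.** **Document check.** I looked for a motion term in each preprocessing step, test and covariate list that bears on connectivity. Sequence 3 has realignment and ICA. Sections 2.3.6.7 and 2.5.10 have none. By contrast, Sequence 1 does fix a nuisance covariate, total intracranial volume, for all volumetric analyses. The plan states no figure on motion, so there is none to reproduce.

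**Inputs from the article.** Two-sided 5% level (stated in section 2.3.6.7, taken to hold for Phase 3 as well); 40 per group (section 2.3.5). Phase 3 is taken as n = 40, because its objective names participants with obesity and diabetes.

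**Inputs assumed, because the article gives neither:**

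- d, the motion shift: in Phase 3 the mean change in motion divided by the SD of that change; in Phase 1 the group difference in SD units. Range 0 to 0.8.
- r, the correlation left after cleaning: in Phase 3 between motion change and connectivity change; in Phase 1 between motion and connectivity within group. Range 0 to 0.4.

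**Formula.** With no true neural effect, let outcome = r × motion + √(1 − r²) × noise, with unit variances. The spurious standardised effect is r × d. The rejection probability comes from the noncentral t with

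- paired, n = 40: noncentrality = r × d × √40 = 6.32 × r × d, 39 df;
- two groups of 40: noncentrality = r × d × √20 = 4.47 × r × d, 78 df.

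Worst corner: 0.4 × 0.8 = 0.32, giving noncentralities of 2.02 and 1.43.

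| r | d | r × d | Paired, n = 40 | 40 vs 40 |
|---|---|---|---|---|
| 0 | any | 0 | 5.0% | 5.0% |
| 0.1 | 0.2 | 0.02 | 5.2% | 5.1% |
| 0.1 | 0.8 | 0.08 | 7.8% | 6.4% |
| 0.2 | 0.3 | 0.06 | 6.6% | 5.8% |
| 0.3 | 0.5 | 0.15 | 15.2% | 10.2% |
| 0.3 | 0.8 | 0.24 | 31.6% | 18.5% |
| 0.4 | 0.8 | 0.32 | 50.6% | 29.3% |

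These are rates per connectivity test. Section 2.5.3 makes all Phase 1 participants eligible for Phase 3. If all 80 entered, r = 0.3 with d = 0.5 would give 26.3% instead of 15.2%, because a larger sample detects the same bias more often.

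**After adjustment.** I simulated the paired case at n = 40, testing the intercept with motion change in the model (at least 20,000 repetitions per case). The false-positive rate went from 9.0% to 4.9% (r = 0.3, d = 0.3), from 15.5% to 4.9% (r = 0.3, d = 0.5), and from 50.6% to 4.9% (r = 0.4, d = 0.8). At r = 0.3 the standard error of the change grew by roughly 1% at d = 0.3 and 24% at d = 0.8. The simulation takes motion to act linearly and to be measured without error.

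**The case against.** **A condensed article may leave this out.** Motion summaries, censoring limits and second-level covariates often sit in an imaging manual or analysis plan. The preprocessing steps are introduced as inclusions, and the statistics sections are not exhaustive: intracranial volume is a covariate under Sequence 1 but appears in neither. This stands against any complaint that a motion threshold is missing, and I make none. It does not remove the point, because the article names its tests, names its covariates, and fixes a nuisance term for volumetry while giving none for connectivity.

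**Motion is already handled in several ways.** True: padding, instruction, realignment and ICA all reduce it. If together they remove nearly all of it, the rate stays at 5%. But the analysis as described gives no way to show that they did.

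**A reader might infer that the yoga programme trains people to lie still, so motion will fall.** The documents do not say so. They describe postures, breathing, relaxation and concentration, and give no motion data. Direction and size are unknown. Nor does the article give any reason to expect motion to differ between the two obese groups in Phase 1.

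**A reader might also infer that a control arm would not help.** That goes too far. A control arm could cancel scan familiarity; only a motion change produced by the practice itself would remain.

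**A reader might extend the point to DTI.** Sequence 2 already specifies subject motion correction with outlier rejection, so the case there is much weaker and I do not press it.

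**Adjustment has its own bias.** Motion at six months is measured after the intervention. If practice affects both motion and connectivity, adjusting may remove part of a real effect. This stands, and it is why the adjusted Phase 3 result should accompany the unadjusted one and not replace it.

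**Conclusion.** The point holds for resting-state connectivity, in conditional form. The stated tests carry any systematic difference in residual motion straight into the effect estimate, in a primary outcome of both phases and, in Phase 3, without a control group.

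The harm is possible, not shown. Over the assumed ranges the false-positive rate lies between 5% and about 51% for the paired test, and between 5% and about 29% for the group test. The upper figures need both assumptions at their extremes and should not be read as expected values. A middle case (r = 0.3, d = 0.5) gives 15% and 10%. The change is worth making because it is cheap and because, without it, a positive connectivity result cannot be separated from a change in scanner behaviour. Motion adjustment does not cure the wider weakness of an uncontrolled pre-post comparison.

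**What to change.** 1. Derive mean framewise displacement for each resting-state scan from the existing realignment step, and tabulate it by group (Phase 1) and by visit (Phase 3).
2. Phase 1: add it as a covariate in the connectivity group comparison, which then becomes a linear model with group and motion in place of the unadjusted t-test or Mann-Whitney test.
3. Phase 3: pre-specify a sensitivity analysis using the mixed model of section 2.5.10 with visit-specific motion added, reported beside the unadjusted result.
4. State in advance that a connectivity change will be described as neuroplasticity only if it persists in the motion-adjusted analysis.

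The cost is a few lines of analysis, with no new data. The price is some precision in Phase 3 (roughly 1% to 24% on the standard error in the cases above) and possible over-adjustment, since motion after the intervention may itself be affected by it. Showing both results lets the reader judge. If an unseen imaging or analysis plan already contains these steps, a sentence in sections 2.3.6.7 and 2.5.10 would settle the matter.
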